### Outcomes and data collection

Several outcomes will be measured and compared between mindfulness and control groups to assess the effects of the course. The primary outcome will be a self-reported global measure of psychological distress assessed during the examination term, the most stressful period of Cambridge students' academic year. Secondary outcomes are exploratory assessments that may help to describe mindfulness' effects in more focused ways. Outcomes are listed in table 1.

**Table 1 BMJOPEN2016012300TB1:** MSS study outcomes

Outcome	Source/measure	Variable type	Collection points
Use of mental health services	Self-reported	Nominal	One-year follow-up
Use of University Counselling Service	Routinely collected	Nominal	Baseline, 1-year follow-up
Perceived impact of problems on academic performance	Self-reported	Ordinal	Examination term
Examination grades and rankings	Routinely collected	Ordinal	Examination term
Special circumstances requests for examinations	Routinely collected	Nominal	Examination term
Inability to sit examinations (intermissions and degrading)	Routinely collected	Nominal	Examination term
Psychological distress	Self-reported: CORE-OM	Treated as interval	Baseline, postintervention, examination term, 1-year follow-up
Well-being	Self-reported: WEMWBS	Treated as interval	Baseline, postintervention, examination term, 1-year follow-up
Altruism	Behavioural	Ordinal	Postintervention, examination term, 1-year follow-up
Coping	Self-reported	Ordinal	Baseline (Lent), examination term
Physical activity	Behavioural (sensor)	Ratio	Baseline (Lent), examination term
Sleep times	Behavioural (sensor)	Ratio	Baseline (Lent), examination term

CORE-OM, Clinical Outcomes in Routine Evaluation Outcome Measure; MSS, Mindful Student Study; WEMWBS, Warwick-Edinburgh Mental Well-being Scale.

Psychological distress will be measured using the Clinical Outcomes in Routine Evaluation Outcome Measure (CORE-OM), a 34-item generic questionnaire which was designed to assess efficacy and effectiveness across multiple disciplines offering psychological therapies, and has been widely used with UK university students. It is scored on a five-point scale ranging from 0 (not at all) to 4 (most or all the time). The total score range is 0–136; this is usually divided by number of completed items to form a total mean score. CORE-OM has good convergent validity, internal and test–retest reliability and sensitivity to change.^14^

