Day-to-day coping during the examination period will be assessed by applying ecological momentary assessment based on the cognitive appraisal theory of coping.^16^ Every morning for 2 weeks, six questions will be asked about coping with academic stress on the previous day. These data will also be collected for a week at baseline from the participants recruited in January 2016. Motivational relevance (How motivated did you feel by academic matters yesterday?, How stressed did you feel by academic matters yesterday?), problem-focused coping potential (Did you study as much as you had planned yesterday?, Did you take as many breaks from study as you had planned yesterday?) and emotion-focused coping potential (How satisfied with yourself are you about the amount you studied yesterday?, How satisfied with yourself are you about the breaks from study you took yesterday?) will be assessed. Participants with an Android smartphone will be able to install a free application (‘EasyM’, developed by the University of Cambridge Computer Laboratory^17^) that will send notifications and display the questions. Other participants will receive a text message notification with a link to an online survey. In order to see how disrupted students' healthy routines become during the examination period, physical activity and sleep pattern data will be passively collected from Android users by the EasyM app using movement sensors (built-in accelerometer) for 2 weeks.

In view of evidence that mindfulness may stimulate altruism,^18^ and that altruistic actions are associated with increased well-being,^19^ we are exploring altruistic behaviour differences between groups. A sum of money in the form of Amazon vouchers will be offered to participants after completing each questionnaire (£3 for postintervention and 1-year follow-up questionnaires, £5 for the examination term questionnaire which will measure the primary outcome). A choice will be given as to whether to keep the token or to donate it to a local mental health charity. This will constitute an objective measure of altruism.

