### Inducements for participation

There will be no inducements for completing the mindfulness courses. However, to promote participant retention and as a token of appreciation for completing all the study questionnaires, a total of £11 will be available to each student across the study in the form of Amazon vouchers as explained above. In addition, there will be a prize draw of 5×£100 Amazon vouchers among those who complete 50% or more smartphone questions plus all the questionnaires. Students who complete 50% or more smartphone notifications will be offered individual feedback on their coping, sleep and physical activity patterns after the study ends.

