### Statistical methods

The primary analysis will consist of an intention-to-treat analysis comparing the primary outcome, CORE-OM during the examination period, between arms adjusted for baseline scores, routine demographics and timing of receipt of intervention relative to examinations (as some will have done the course during Michaelmas 2015 and others during Lent 2016). Multiple imputation will be used as long as there are <40% missing data in the corresponding variable to ensure validity of imputations and will be applied only to variables with expected missing completely at random and missing at random patterns (ie, when there are no reasons to think that the pattern may be missing not at random). This imputation will take account of other CORE-OM data points and routinely collected demographics. We will also conduct a per-protocol analysis (minimum dose assumed to be 50% attendance of sessions^24^) excluding individuals in the control group who have engaged in meditation elsewhere during the follow-up period preceding outcome measurement.

Outcomes measured at three time points (CORE-OM, WEMWBS and altruism, measured at postintervention, examination period and 1-year follow-up) will be analysed using a repeated measures design with a treatment by time interaction term to study their trajectories through the academic year and to determine whether differences (ie, intervention effects) were consistent over time. Repeated measures analyses will also be performed with ecological momentary assessment data to study outcome trajectories, pattern changes during the examination period and differences between arms.

CORE-OM and WEMWBS data will be combined to explore the broader spectrum of distress/well-being if taken as a continuum.^25^ Subscales of the CORE-OM (subjective well-being, problems symptoms, functioning, risk/harm) will also be explored as secondary outcomes, and results reported with and without correction for multiple testing. Multilevel models will be used to assess academic degrees and academic rankings as any student may sit more than one examination.

The following predefined subgroup analyses will be conducted on the primary outcome by using interaction tests:^26^

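### The altruism choice is over £5 at the examination term but £3 at the other two visits, so altruism time contrasts involving the examination term are confounded with the stake

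*Protocol article*

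**What the plan says.** All references are to the Protocol article.

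- **Outcomes and data collection** defines the measure: "A choice will be given as to whether to keep the token or to donate it to a local mental health charity". The stated interest is that "we are exploring altruistic behaviour differences between groups". The voucher values, all in pounds, are "3 for postintervention and 1-year follow-up questionnaires, £5 for the examination term questionnaire which will measure the primary outcome".
- **Table 1** lists altruism at "postintervention, examination term, 1-year follow-up", with no baseline measurement. The same section describes secondary outcomes as exploratory.
- **Inducements for participation** says that "a total of £11 will be available to each student across the study".
- **Statistical methods** names altruism among the outcomes for longitudinal analysis: "Outcomes measured at three time points (CORE-OM, WEMWBS and altruism, measured at postintervention, examination period and 1-year follow-up". These are to be analysed by a "repeated measures design with a treatment by time interaction term to study their trajectories through the academic year", and also to see whether intervention effects stay the same across the visits. Linear mixed models are the stated method.

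None of these sections mentions that the stake differs between visits.

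**The concern.** The voucher does two jobs. It rewards completion of the questionnaire, and it is the instrument that measures altruism. Raising it at the examination term is sensible for the first job, because the primary outcome is collected there. For the second job it changes the instrument at one of three visits: giving up £5 is a different decision from giving up £3.

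The planned analysis compares visits with one another. A fall or rise in donations at the examination term could reflect the time of year, the larger sum, or both. If the larger sum acts differently in the two arms, the treatment-by-time term would pick that up as a mindfulness effect that changes at the examinations. At stake is the reading of one visit of one exploratory outcome.

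**Working it through.** **1. The plan's own figure.** 3 + 5 + 3 = 11, which matches the £11 under Inducements for participation. The stakes are therefore £3, £5 and £3.

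**2. Can a model separate stake from visit?** Let E = 1 at the examination term and 0 otherwise, and A = 1 for the mindfulness arm. Then:

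- stake = 3 + 2E
- A × stake = 3A + 2(A × E)

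The saturated model for two arms and three visits has six columns: intercept, arm, two visit indicators and two arm-by-visit terms. Its rank is 6. Adding stake (7 columns) leaves the rank at 6, and adding arm-by-stake (8 columns) still leaves it at 6. Stake is fully aliased with the examination-term indicator, and arm-by-stake with the arm-by-examination-term interaction. No covariate adjustment can undo this.

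**3. Which contrasts are affected?**

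| Contrast | Stakes compared | Affected? |
|---|---|---|
| Between arms, within any visit | equal | no |
| Postintervention v 1 year, and its treatment interaction | £3 v £3 | no |
| Examination term v either other visit | £5 v £3 | yes, by any stake effect |
| Treatment interaction for the examination term | £5 v £3 in both arms | only if the stake effect differs by arm on the model scale |

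**4. Illustrative size: change pooled over arms.** Inputs: 440 respondents (550 less 20% loss, Sample size section). Assumed: a yes/no choice, donation p = 0.40 at £3, donation q at £5, within-person correlation ρ of 0.5 to 0.7, and no true change in altruism.

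SE = √[p(1−p) + q(1−q) − 2ρ√(p(1−p)q(1−q))] / √440

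- q = 0.35: the variance term is 0.2338 (ρ = 0.5) or 0.1404 (ρ = 0.7), so SE = 0.0231 or 0.0179, and z = 0.05/SE = 2.17 or 2.80. The probability of two-sided significance at 0.05 is 58% or 80%.
- q = 0.30: z = 4.42 or 5.69, and the probability is above 99%.

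**5. Illustrative size: interaction.** With 220 per arm and the same variance terms, SE = √(2 × 0.2338/220) = 4.6 points or √(2 × 0.1404/220) = 3.6 points. Assume donation at £3 of 40% in control and 50% with mindfulness.

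- Stake effect of −10 points in both arms: a false 10-point fall over time, but an interaction of 0.
- Stake effect equal on the logit scale (−0.2 to −0.8): a linear model shows an interaction of −0.3 to −2.0 points. At 2.0 points, z = 2.0/4.6 to 2.0/3.6, about 0.43 to 0.56, significant about 7% to 9% of the time against a nominal 5%.
- Stake effect of −10 points in control and −5 or 0 with mindfulness: an interaction of 5 or 10 points, which the data could not tell apart from an examination-period effect.

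**6. With one stake at all visits.** Stake is then a constant and is absorbed into the intercept, so the visit and interaction terms no longer carry it.

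**The case against.** The strongest reply is that the stated interest in altruism is the difference between arms, and both arms face the same stake at every visit. Each randomised within-visit contrast is therefore valid. That stands, but Statistical methods goes further and plans comparisons across visits, and the point concerns those.

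Second, the interaction is the main inferential target, and a stake effect common to both arms cancels or nearly cancels there. This also stands. A reader might take the 58% to 80% figures as the risk of a false treatment-by-time result. They are not: they concern only the change pooled over arms. A sizeable false interaction needs a stake effect that differs by arm, for which the document gives no evidence either way.

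Third, a reader might infer that the whole altruism time analysis is lost. It is not, because postintervention and 1 year share the £3 stake, so that comparison and its interaction carry no stake confounding.

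Fourth, the protocol nowhere says that a change in giving will be attributed to examination stress. With no baseline, a repeated choice, attrition and two recruitment waves, such an attribution would be weak even with equal stakes. That is correct. Equal stakes remove one explanation, not all of them.

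Finally, the larger voucher is a disclosed choice that favours retention for the primary outcome. That is a good reason for £5 at that visit, but it does not require the whole £5 to be the donation stake. Nor can the matter be left to an analysis plan that is not shown, since no model can separate two aliased terms.

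**Conclusion.** The point holds, in limited form. The aliasing in step 2 is exact, follows from the stated voucher amounts and visits, and needs no assumption. It is confined to altruism contrasts that involve the examination term: the time contrast takes up any stake effect in full, and the interaction takes it up only so far as the effect differs by arm on the model scale.

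The size and direction of any stake effect are unknown, and the donation rates and correlations are assumptions. The probabilities therefore show what could happen and do not predict it. Because altruism is exploratory and the CORE-OM analysis is untouched, this is a minor, worthwhile improvement and no threat to the trial's main conclusion.

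**What to change.** **If vouchers are not yet issued:** offer the same £3 keep-or-donate choice at all three visits. At the examination term, pay a further £2 as a completion voucher outside the choice. Disclose it in the total incentive but issue it only after the choice is made, so that students do not already hold an extra £2 when they decide. The incentive at that visit stays at 3 + 2 = £5, and the total at 3 + (3 + 2) + 3 = £11. The cost is a change to the voucher screen in the online questionnaire and two vouchers at one visit. Students who expect the extra £2 might still be slightly influenced by it, but the sum given up would be constant.

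**If vouchers have been issued:** keep the data and add a sentence to the analysis plan. Report altruism as arm contrasts within each visit, plus the postintervention versus 1-year time and treatment-by-time contrasts. State that time or interaction effects involving the examination term will not be interpreted as due to the examination period, because the stake also differed. This costs nothing and keeps every comparison that the stake leaves clean.

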### Sample size

The minimum sample size required was calculated to detect a 0.3 SD change in psychological distress with CORE-OM, the primary outcome. This change constitutes a small difference, but is reasonable for a relatively short mindfulness course, and attractive if this shift happens at a community rather than a clinical level.^20^

A study of a non-clinical sample (746 students from two UK universities plus a community sample of 360 people) found a mean total score of 0.76 points and a SD of 0.59 points.^21^ To detect a change of 0.3 SDs at p<0.05 with 90% power, 550 students (275 per arm) are estimated to be needed, allowing for 20% loss to follow-up as informed by previous studies (eg, Warnecke *et al*^22^).

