**Methods and analysis:**

At least 550 University of Cambridge students free from active crises or severe mental illness will be randomised to joining an 8-week mindfulness course or to mental health provision as usual (one-to-one allocation rate). Psychological distress will be measured using the Clinical Outcomes in Routine Evaluation Outcome Measure at baseline, postintervention, examination term and 1-year follow-up. Other outcomes are use of mental health services, inability to sit examinations or special circumstance requests, examination grades, well-being, altruism and coping measured with ecological momentary assessment. Outcome assessment and intention-to-treat primary analysis using linear mixed models adjusted for baseline scores will be blind to intervention allocation. We will also conduct per-protocol, subgroup and secondary outcome analyses. An Independent Data Monitoring and Ethics Committee will be set up. We will systematically monitor for, and react to, possible adverse events. An advisory reference group will comprise student representatives, members of the University Counselling Service and other student welfare staff.

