### Trial design

The study will be a pragmatic randomised controlled evaluation with two parallel arms and a one-to-one allocation rate testing the superiority of mindfulness training provision to no provision. University of Cambridge students will be randomised to joining a mindfulness course during the term they are starting plus mental health provision as usual (PAU), or to PAU alone. PAU comprises access to individual counsellors, mental health advisors and psychiatrists at the University of Cambridge Counselling Service (UCS), as well as access to welfare staff in the University colleges (this provision varies across colleges, but can include college nurse, counsellor, welfare officer or tutor) and National Health Services (NHS). Those allocated to PAU alone will be offered a mindfulness course 1 year later, providing they are still students at the University.

The mindfulness intervention was offered for two terms before study initiation; this allowed the intervention to become established before evaluating it, and provided feasibility and acceptability data. The present proposal is partly based on the experience during those two terms. Interest in the courses doubled teaching capacity. An opportunistic randomised evaluation was therefore considered reasonable.

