By degree, as most have examinations during the examination term but some do not;By year of study, to explore whether results differ for last year students, a different subpopulation as control group final year students will not be offered mindfulness a year later;By baseline CORE-OM: those initially worse may drive change;By gender: there is evidence of differential impact;^10^By amount of home practice during and after course in intervention group participants;By prior meditation experience (prior 8-week course or +50 hours spent meditating in the past—an 8-week course translates into 10–50 hours) as only novices may experience a change.

In order to assess how our sample compares against the student population in the UK, demographic and normative well-being/distress data will be obtained from the literature and compared with baseline values in our sample. A comparison of our baseline data with the profile of students attending the University Counselling Service will also be performed where possible to evaluate where our sample lies in the range between community and clinical student samples.

All statistical analyses will be conducted at an α level of p=0.05 (two-sided). Linear mixed models will be used for the analyses. Assumptions will be tested and diagnostic plots will be explored to assess model fit. Descriptive statistics for continuous variables will be summarised using mean/SD and median/IQR. Discrete variables will be summarised by proportions.

It is expected that the clustering effect will be negligible: although this is a group intervention, the work is highly personal, all the courses are taught by the same teacher, each course includes students from different colleges and courses, and the ‘session hopping’ option introduces variability. However, we will compute intraclass correlation by analysing session attendance patterns to see whether there is any clustering effect. If there is one, we will adjust for it using multilevel techniques.

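### The stated inputs for 90% power with 20% loss need about 586 students, not 550; at 550 the unadjusted power is about 88% (minor arithmetic error)

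*Protocol article*

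**What the plan says.** The Sample size section describes the target as a minimum: "The minimum sample size required was calculated to detect a 0.3 SD change in psychological distress with CORE-OM, the primary outcome". It cites a non-clinical sample that "found a mean total score of 0.76 points and a SD of 0.59 points", and then concludes: "To detect a change of 0.3 SDs at p<0.05 with 90% power, 550 students (275 per arm) are estimated to be needed". The same sentence makes clear that attrition is already built into this number, with the words "allowing for 20% loss to follow-up as informed by previous studies".

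Three other places bear on the figure:

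- The Abstract (Methods and analysis) repeats it as a floor: "At least 550 University of Cambridge students".
- Trial design specifies "two parallel arms and a one-to-one allocation rate testing the superiority of mindfulness training provision to no provision".
- Statistical methods sets a two-sided 0.05 level for all analyses. It also plans a primary comparison "adjusted for baseline scores, routine demographics and timing of receipt of intervention relative to examinations".

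The Sample size section mentions no baseline-outcome correlation and no design effect.

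**The concern.** The paragraph gives every input of a standard two-group calculation together with its result, and the two disagree. Nothing needs to be assumed to see this. The discrepancy of 36 to 38 students is larger than rounding up would explain, and it goes in the unfavourable direction.

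What is at stake is the accuracy of two printed statements about the trial's headline minimum: the 90% power and the 20% loss allowance. A team that checks retention against 20% would think the stated power safe, although on the stated inputs the allowance is used up at about 15% loss.

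**Working it through.** **Inputs**

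| Input | Value | Place in the protocol |
|---|---|---|
| Difference | 0.3 SD | Sample size |
| SD | 0.59 points (cancels, since the difference is in SD units) | Sample size |
| Power | 90% | Sample size |
| Loss | 20% | Sample size |
| Stated N | 550 (275 per arm) | Sample size |
| Significance level | 0.05, two-sided | Statistical methods |
| Allocation | 1:1 | Trial design |

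**Step 1: attempt to reproduce 550.** Number analysed per arm:

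n = 2 × (1.960 + 1.2816)² / 0.3² = 233.5, so 234. The exact t-test gives 235. The total is 468 to 470.

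Inflation for 20% loss:

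- 234 / 0.80 = 292.5, so 293 per arm and 586 in total
- 235 / 0.80 = 293.75, so 294 per arm and 588 in total

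The stated 550 is therefore 36 to 38 short, about 6%.

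**Step 2: other routes to 550**

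| Variant | Total N |
|---|---|
| One-sided 0.05 (contradicts Statistical methods): 191 per arm, 382 / 0.80 | 478 |
| Multiplying by 1.2 instead of dividing by 0.8: 468 × 1.2 or 470 × 1.2 | 562 or 564 |
| Difference rounded up from 0.177 to 0.18 points (0.305 SD; not in the protocol): 226 per arm, 283 after loss | 566 |
| Both of the last two together: 226 × 1.2, so 272 per arm | 544 |
| 15% loss: 468 / 0.85 | 550.6 |

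Only a 15% loss gives 550, and the text says 20%.

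**Step 3: what 550 delivers with 20% loss.** Analysed per arm: 275 × 0.80 = 220.

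- Standardised effect: 0.3 × √(220/2) = 3.146
- Power: Φ(3.146 − 1.960) = Φ(1.186) = 88.2% (t-test 88.1%)
- Difference detectable with 90% power: 3.2415 × √(2/220) = 0.309 SD. That is 0.309 × 0.59 = 0.182 CORE-OM points, against 0.3 × 0.59 = 0.177.

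**Step 4: loss at which 550 still gives 90%**

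- Normal: 1 − 468/550 = 14.9%
- t-test: 1 − 470/550 = 14.5%

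**Step 5: effect of baseline adjustment.** The correlation r between baseline and outcome is an assumption, because the protocol gives none. Adjustment multiplies the residual SD by √(1 − r²). With 220 per arm and no clustering, 90% power requires √(1 − r²) = 3.146 / 3.2415 = 0.9705, so r is about 0.24 (about 0.25 on the t-test basis).

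| Assumed r | Power at 220 per arm (normal) |
|---|---|
| 0.1 | 88.5% |
| 0.2 | 89.5% |
| 0.25 | 90.1% |
| 0.3 | 91.0% |
| 0.5 | 95.3% |

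**The case against.** The best defence is that the comparison in Steps 1 to 4 is not the one the trial will run. The primary analysis adjusts for baseline CORE-OM, and the protocol itself describes the questionnaire as having good test-retest reliability. A correlation as low as 0.25 between two administrations some months apart would be a cautious assumption. On that view the trial probably has 90% power or more at 550 with 20% loss. This stands as a statement about likely real power. It does not make the printed sentence right, because the Sample size section neither states a correlation nor says that the calculation used one.

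Two further points have some force. The 550 is a floor, so recruitment may exceed it. Capacity would allow that: seven courses of up to 30 over two waves is 420 places, less up to 60 for students outside the trial leaves 360, which under 1:1 allocation supports about 720 randomised. Multiple imputation is also planned for missing data. Neither repairs the figure. A stated minimum below what its own inputs require is still wrong, and the paragraph makes an explicit loss allowance without relying on imputation.

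Stronger readings are tempting but not supported:

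- **That the trial is materially underpowered, or that a null result could not be trusted.** The shortfall is about 2 points of power in an unadjusted comparison, and the planned adjustment would probably close it.
- **That the authors used 15% loss.** The arithmetic fits, but the protocol does not say so, and the origin of 550 remains conjecture.
- **That the paragraph must also present a range of clustering assumptions.** Clustering is a separate matter. Statistical methods gives reasons for expecting it to be negligible and commits to adjusting if it is found.

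**Conclusion.** The concern holds as a minor arithmetic error. On the protocol's stated inputs, with no baseline correlation and no design effect, about 586 to 588 students would have to be randomised, not 550. At 550 with 20% loss, unadjusted power is about 88% for 0.3 SD. The difference detectable with 90% power moves from 0.300 to 0.309 SD, about 0.005 CORE-OM points on the 0.59 SD. The 90% claim holds at 550 only if loss is at most about 14.5 to 15%.

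The unadjusted results need no assumption beyond the printed inputs. The statement that adjustment would probably recover the gap rests on an assumed correlation of about 0.25 or more and on no clustering. The error lies in how the figure is reported. It does not call the design, the analysis or the recruitment target into question.

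**What to change.** Restate the Sample size paragraph so that the number, the power and the loss agree. Any one of these is enough:

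- 550 randomised, 20% loss, 220 analysed per arm: 88% power for 0.3 SD (90% for 0.31 SD), unadjusted.
- 550 randomised: 90% power for 0.3 SD provided that loss is at most about 14.5%.
- 550 randomised, 20% loss: 90% power for 0.3 SD in the baseline-adjusted analysis, with the baseline-outcome correlation relied on stated (about 0.25 or higher, without clustering).

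The cost is one paragraph of wording and, under the first two options, a slightly less favourable power or loss statement. No extra recruitment and no change to the analysis are required.
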